#### Sample size considerations and statistical analyses

##### Sample size estimation

Sample sizes were calculated using the method developed by Frison and Pocock [37] with the SF-36 PCS as the primary outcome. Because patients are randomized within surgeon, we assume complete randomization of the study subjects to each treatment arm. We used the mean changes of repeated measures to estimate the required sample sizes based on Analysis of Covariance (ANCOVA) method. The mean change is defined as the difference between each subject's mean post-treatment PCS (the mean of 6 and 12 month PCS) and the baseline measurement.

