##### Effect Size

This trial was designed to determine whether the intervention will outperform the control by 4 or more points in the SF36 PCS. This effect size is approximately one-half of the PCS standard deviation and 40% of the mean pre-post PCS TKR change of 10.5 points reported in the PORT study. Based on our pilot data and the national registry of TKR patients, mean post-PCS scores are assumed to be 39.5 and 43.5 for the control and intervention arms, respectively; the standard deviation of post-TKR PCS is estimated as 10.9 for pre-and post-intervention periods and the autocorrelation coefficient between the post treatment measurements across time for PCS is 0.65, and between pre-and post treatment measures is 0.50 [4]. One pre-intervention and two post-intervention measurements were completed (6 and 12 months). Assuming 75 completers per condition after attrition or exclusion due to missing data, the trial is capable of detecting an intervention effect of a change of 4 or more points on the SF36 PCS with statistical power in excess of 0.83 at two-sided significance level of 0.05, or 0.90 at one-sided significance level of 0.05. Secondarily, a 10 point difference in change in WOMAC physical functional scores between the arms can be detected with > 85% power at 5% significance level.

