In the analysis, we will assess possible selection bias by evaluating the equivalence in subjects' socio-demographic characteristics and baseline clinical and behavioral measures between "completers" (i.e., patients participating in 6 and/or 12 month follow-up) and drop-outs. If systematic and significant differences are observed, we will apply proper statistical procedures to account for such informative attrition or missingness. (See below) Differences between completers and drop-outs will be acknowledged as limitations to the generalization of study results.

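### The attrition check counts anyone seen at 6 or 12 months as a completer, so it cannot detect selective loss between the two visits

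*Protocol article*

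**What the plan says.** All references are to the protocol article.

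- **Analysis Plan, paragraph on selection bias.** Completers are "patients participating in 6 and/or 12 month follow-up", and they are compared with drop-outs on socio-demographic and baseline measures. Procedures for informative attrition or missingness are applied only if that comparison shows differences.
- **Analysis Plan, model.** The outcome is PCS change at 6 or 12 months, in a two-class latent mixture model with terms for arm, time and their interaction. The treatment effect is judged on the arm and interaction terms.
- **Sample size estimation.** The sizing quantity is the difference between "each subject's mean post-treatment PCS (the mean of 6 and 12 month PCS) and the baseline measurement".
- **Effect Size.** The power statement opens: "Assuming 75 completers per condition after attrition or exclusion due to missing data". It counts one measurement before and two after the intervention, and gives power above 0.83 two-sided, or 0.90 one-sided, at the 0.05 level. Completer is not defined there.
- **Background and Study Design.** Better function at both 6 and 12 months is hypothesised.

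**The concern.** The comparison of completers with drop-outs decides whether informative missingness is dealt with at all. For that purpose, the group called lost should contain the patients whose outcome is missing. Under the and/or rule it contains only those who missed both visits. Anyone who missed one visit, notably a patient who left after 6 months, is pooled with patients who have full data.

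If patients with, say, poorer emotional health left selectively between 6 and 12 months, the 12 month comparison and the time-by-intervention term would rest on a selected group. The planned check would not show it. Changing the statistical test would not help, because the fault lies in how patients are grouped.

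A lesser point is that the same word, completer, describes the 75 per arm in the power statement, where the calculation assumes both visits.

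**Working it through.** **1. How the rule classifies each visit pattern**

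| PCS at 6 months | PCS at 12 months | Group under the rule | 12 month outcome |
|---|---|---|---|
| yes | yes | completer | present |
| yes | no | completer | missing |
| no | yes | completer | present |
| no | no | drop-out | missing |

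Let b be the number of patients in row 2 and d the number in row 4. The number missing the 12 month outcome is b + d, but the drop-out group holds only d. The b patients enter the comparison on the completer side, so a difference between them and patients who stayed cannot appear as a difference between completers and drop-outs. Row 3 raises the same problem for the 6 month outcome.

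**2. Reproducing the stated power**

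Inputs, all from Effect Size:
- difference 43.5 − 39.5 = 4 points ("mean post-PCS scores are assumed to be 39.5 and 43.5 for the control and intervention arms, respectively")
- SD 10.9 ("the standard deviation of post-TKR PCS is estimated as 10.9 for pre-and post-intervention periods")
- correlation 0.65 between post-operative measures and 0.50 between pre- and post-operative measures
- 75 per arm

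Frison–Pocock ANCOVA with one pre- and two post-operative measures:
- variance factor = (1 + 0.65)/2 − 0.50² = 0.825 − 0.25 = 0.575
- residual SD = 10.9 × √0.575 = 8.265
- SE = 8.265 × √(2/75) = 1.350, and 4/1.350 = 2.964
- two-sided power = Φ(2.964 − 1.960) = 0.842 (stated: above 0.83)
- one-sided power = Φ(2.964 − 1.645) = 0.906 (stated: 0.90)

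Both figures reproduce. With one post-operative measure for everyone, the factor is 1 − 0.50² = 0.75 and two-sided power is 0.737, which does not match. The stated figure therefore rests on both visits for all 75.

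**3. If some of the 75 had only one visit**

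The share s is not given, so 10 to 30% is assumed. One-visit patients are kept with their single value, and the 4-point effect is taken to be the same at both visits. Two approximations:
- adding information: per-arm information = 75 × [(1 − s)/0.575 + s/0.75] / 10.9²
- averaging variance factors: factor = (1 − s) × 0.575 + s × 0.75, with n = 75

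| s | Adding information | Averaging factors |
|---|---|---|
| 0 | 0.842 | 0.842 |
| 10% | 0.834 | 0.831 |
| 20% | 0.825 | 0.820 |
| 30% | 0.815 | 0.810 |

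Worked example at s = 10% (adding information): 75 × (0.9/0.575 + 0.1/0.75) = 127.4; SE = 10.9 × √(2/127.4) = 1.366; power = Φ(4/1.366 − 1.960) = 0.834.

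**The case against.** The and/or definition suits the planned model. A longitudinal model of change at 6 or 12 months can use a patient with one visit, so it is natural to call anyone who contributes data a completer and anyone who contributes none a drop-out. The Abstract also places the powered difference at six months, and on that wording a patient lost afterwards has the main time point. The selection-bias paragraph speaks of missingness as well as attrition, and a fuller document might tabulate it by visit.

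Part of this stands. One-visit patients are not lost to the analysis, and patients lost to both visits would still be seen by the check. But the article does not leave the grouping open. It states a rule and makes the handling of missing data depend on it. Being usable in the model is not the same as having a 12 month outcome, and the check is meant to reveal selective absence of outcomes.

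A reader might go further and infer that one-visit patients count toward the 75 without having the powered endpoint, so that the trial is underpowered. Dropping such patients from the 75 would give power of 0.803, 0.755 and 0.698 at 10, 20 and 30%. The document does not support that inference:

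- The 75 are stated as remaining after exclusion for missing data, which can well mean patients with both values.
- The and/or definition appears later and serves a different purpose.
- Nothing in the article says one-visit patients are dropped.
- With 90 per arm enrolled (half of 180), a 30% one-visit share leaves 75 × 0.70 = 52.5 with both visits. Then 37.5/90, about 42%, would be missing at least one visit, against an assumed loss of no more than 15%.

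**Conclusion.** The point holds for the attrition check. As defined, the check cannot detect selective loss between 6 and 12 months, so that loss cannot trigger the missing-data procedures. This follows from the stated rule without any assumption about numbers. How much bias could result cannot be given, because the article does not state how many patients are expected to miss one visit.

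No power deficit is shown. The stated power is correct when all 75 per arm have both values (0.842 two-sided). If 10 to 30% of them had one visit and were kept in the model, power would be about 0.83 to 0.81, still above the 80% design claim in the Abstract. Those figures assume equal effects at both visits and approximate the latent-class model by a simple repeated-measures comparison. What remains on the power side is a clarification: say what completer means for the 75.

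**What to change.** - **Analysis Plan, selection-bias paragraph.** Replace the single comparison with two: baseline characteristics of patients with and without PCS at 6 months, and separately at 12 months. Let either comparison trigger the procedures for informative missingness.
- **Effect Size.** State that the 75 per arm are patients with both post-operative PCS values, which is the basis on which the stated power reproduces.

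No change of model is needed on this account, since the planned longitudinal model can already use patients with one visit. The cost is a few words, one additional table from data already collected, and possibly a lower reported number of completers.

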**Methods/Design:**

This randomized clinical trial (RCT) will test the efficacy of a theory-based telephone-delivered Patient Self-Management Support intervention that seeks to enhance adherence to independent exercise and activity among post- TKR patients. The intervention consists of 12 sessions, which begin prior to surgery and continue for approximately 9 weeks post-TKR. The intervention condition will be compared to a usual care control condition using a randomized design and a probabilistic sample of men and women. Assessments are conducted at baseline, eight weeks, and six- and twelve- months. The project is being conducted at a large healthcare system in Massachusetts. The study was designed to provide greater than 80% power for detecting a difference of 4 points in physical function (SF36/Physical Component Score) between conditions (standard deviation of 10) at six months with secondary outcomes collected at one year, assuming a loss to follow up rate of no more than 15%.

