### Recruitment, baseline assessment and randomization

The study coordinator recruits patients by reviewing a list of patients each week who are scheduled for upcoming TKR surgery, assessing patient's eligibility, calling patients to introduce the study and then mailing the consent form. The coordinator then follows up via telephone call. Patients complete and mail back a baseline assessment that includes the SF-36, the Pre-Surgery WOMAC, and a modified arthritis and exercise Self-Efficacy Scale. In addition, participants wear an ankle accelerometer (Step Activity Monitor) for four continuous days (at least one weekend day), and complete an exercise log.

Upon completing the baseline assessment, each patient is randomized into the Patient Self-Management Support intervention or to a usual care (control) condition. The study uses a stratified simple random sampling (S-SRS) of TKR patients to assure that participants represent subgroups of patients who may respond differently to the intervention. Patients are stratified by gender (two categories), BMI (three categories, < 30, 30-35, and > 35), and emotional health (SF36/Mental Composite Score; MCS) (three categories, < 45, 46-60, and > 60). This sampling scheme ensures that the sample includes wide variation in pre-operative BMI and MCS and gender balance. The categories are based on the distribution of pre-operative measures in a national sample. There are 2 × 3 × 3 = 18 strata in total. Within each stratum, 5 patients are randomized to intervention group and 5 to control group. The order of the two blocks is randomly permuted. Total target enrollment for the trial is 180 patients.

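### Missing data are addressed only if a baseline significance test fires, and that test cannot show whether loss depends on recovery or differs by arm

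*Protocol article*

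**What the plan says.** The Analysis Plan section of the Protocol article models post-operative change in PCS with a two-class mixture model or GLLAMM. The model has terms for arm, time and their interaction, and adjusts for baseline function, gender and BMI among other covariates.

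The section then turns to attrition. Completers, defined as "patients participating in 6 and/or 12 month follow-up", are compared with drop-outs on social, clinical and behavioural measures taken at baseline. The rule follows: "If systematic and significant differences are observed, we will apply proper statistical procedures to account for such informative attrition or missingness". The procedures are not named. A parenthetical pointer refers the reader further on, but the next section is the cost analysis. The paragraph ends: "Differences between completers and drop-outs will be acknowledged as limitations to the generalization of study results". Nothing is said about arm.

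Three other places bear on the size of the problem. The Effect Size section reads: "Assuming 75 completers per condition after attrition or exclusion due to missing data". The recruitment section reads: "Total target enrollment for the trial is 180 patients". The abstract assumes loss to follow-up of at most 15%.

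**The concern.** The rule is a pre-test: a significance test on baseline data decides whether missingness is dealt with at all. It has four weaknesses.

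- **It looks at the wrong data.** Loss is informative when it depends on the unseen outcome, for example poor recovery or disengagement after surgery. Baseline measures cannot exclude that.
- **It does not refer to arm.** Bias in a randomised comparison arises when selection differs between arms. One arm has 12 coaching sessions and the other has usual care, so a difference is possible.
- **It has poor operating characteristics.** Few drop-outs give low power per variable, while many variables give frequent chance findings. The article does not say what makes a difference systematic.
- **It makes the method depend on the data.** How the primary effect is estimated would be settled only after the test result is known.

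The closing sentence also treats differences as a limit on generalization, whereas selective loss can bias the treatment contrast itself.

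**Working it through.** **Inputs from the article.** Enrolment 180; 75 completers per arm; loss at most 15%; target 4 PCS points; SD 10.9; correlation 0.65 between post-operative measures and 0.50 between pre- and post-operative measures; one pre- and two post-operative measures.

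**1. The plan's own power figure.** Frison-Pocock ANCOVA: effective SD = 10.9 × √((1 + 0.65)/2 − 0.50²) = 10.9 × √0.575 = 8.265. With 75 per arm and a 4-point difference, power is 0.842 two-sided and 0.906 one-sided at 0.05. The stated figures (above 0.83, and 0.90) reproduce, so the sample size is not in question here.

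**2. Number of drop-outs.** 180 − 2 × 75 = 30 (16.7%). At 15% loss, 0.15 × 180 = 27.

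**3. Power of the baseline check, per variable.** Two-sample t-test, two-sided 0.05. The standard error in SD units is √(1/150 + 1/30) = 0.200, or √(1/153 + 1/27) = 0.209.

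| True difference | 150 v 30 | 153 v 27 |
|---|---|---|
| 0.2 SD | 17% | 16% |
| 0.3 SD | 32% | 30% |
| 0.4 SD | 51% | 48% |
| 0.5 SD | 70% | 66% |

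For 80% power the difference must be about (1.96 + 0.84) × 0.200 = 0.56 SD, or 0.585 SD with 27 drop-outs. Because one visit is enough to count as a completer, the drop-out group may be smaller than 27. With 18 (10% loss, an assumption), power is 22.5% at 0.3 SD and 36% at 0.4 SD.

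**4. Chance triggers.** The number of variables tested is not given. If k independent variables are each tested at 0.05, the chance of at least one significant result without any selection is 1 − 0.95^k: 40% for k = 10 and 64% for k = 20. About 18 baseline measures can be counted in the article. With k = 18 the chance is 1 − 0.95^18 = 60% without selection, and 1 − 0.68 × 0.95^17 = 72% when one variable truly differs by 0.3 SD. A rule that fires 60% of the time without selection and 72% with it barely discriminates. Correlation between the variables would lower the chance-trigger figures.

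**5. Size of bias (illustration; the deficit is assumed).** Suppose 15% of the intervention arm is lost, the lost patients average d PCS points below that arm's completers, and loss in the control arm causes no bias. The completer contrast is then overstated by 0.15 × d:

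- d = 3: 0.45 points; 0.45/4 = 11% of the target.
- d = 6: 0.90 points; 0.90/4 = 22.5% of the target.

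These figures are before baseline adjustment.

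**6. Does the trigger fire when it should? (simulation under assumed drop-out models)** 4,000 runs of 180 patients with the article's SD and correlations, a true effect of zero, and 17% to 20% loss in the selective scenarios. The log-odds of drop-out change by 0.7 to 1.0 per 10.9 PCS points. The trigger is a pooled test of baseline PCS, and the estimate is completer ANCOVA.

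| Drop-out depends on | Trigger fires | Bias (points) | Type I error |
|---|---|---|---|
| Outcome, intervention arm only | 14% to 24% | 0.75 to 1.07 | 8.5% to 12.8% |
| Outcome, opposite directions by arm | 5% | 1.5 to 2.2 | 20% to 37% |
| Baseline PCS, opposite directions by arm | 6% to 7% | about 0 | about 5% |

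The second row is a deliberately hard case: there the test fires at only its null rate. The third row shows that baseline adjustment removes the bias when loss depends on baseline PCS alone.

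**The case against.** Four objections carry weight.

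- **A reader might infer that a completer analysis is the default.** The article does not say so. The words "after attrition or exclusion due to missing data" belong to a sample-size assumption, not to an analysis rule. The planned longitudinal model could be fitted by likelihood to all available records, and a patient with one of the two visits counts as a completer. What remains is that a patient with neither visit has no 6- or 12-month change score.
- **A reader might infer that the arms will be pooled and loss by arm left unreported.** The article is silent on this, and a condensed article often leaves such reporting to the full protocol. The sound point is narrower: the trigger as written does not refer to arm.
- **A reader might infer that the test will probably come out non-significant.** Step 3 shows that only for a single variable. Over many variables step 4 points the other way. The defect is that the rule is unreliable in both directions.
- **The bias figures are not derived from the article.** This is correct. It gives no drop-out deficit and no evidence that loss will differ by arm, so the 22.5% is one end of an assumed range and not a forecast. The planned adjustment for baseline function would remove any part of the bias explained by baseline PCS.

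It can also be said that the pointer to later text shows the procedures were described in a fuller document. Their absence here is therefore no fault. The pointer does not cure the rule, however, because the condition for using the procedures is fixed in the article itself.

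**Conclusion.** The concern holds as a criticism of the trigger. Making missing-data handling conditional on a significant baseline difference between completers and drop-outs is unsound, since no such result can show that loss is unrelated to recovery or to arm. Under the article's own numbers the check has about 30% to 32% power per variable at 0.3 SD and 48% to 52% at 0.4 SD. Under assumed independence of 10 to 20 variables it fires by chance 40% to 64% of the time. The possible harm is illustrated by 0.45 to 0.9 PCS points (11% to 22.5% of the target) before baseline adjustment, resting on an assumed 3- to 6-point deficit and 15% selective loss in one arm. The harm arises mainly when loss depends on outcome or on unadjusted factors. The article does not support the stronger statement that the primary analysis is a completer analysis. This should be changed, but it does not invalidate the design.

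**What to change.** 1. Delete the significance-test trigger.
2. State that the primary model in the Analysis Plan section is always fitted by likelihood to all randomised patients, using every available post-operative PCS (including 8 weeks if PCS is recorded then). Adjust for baseline PCS and all three stratification factors; gender and BMI are already listed, so MCS is the addition.
3. Always report loss to follow-up by arm.
4. Pre-specify one delta-adjusted multiple-imputation sensitivity analysis that worsens missing intervention-arm PCS over a stated range, for example 0 to 6 points to cover the illustration above. This step is needed because the likelihood model alone does not correct outcome-dependent loss, and it gains almost nothing from patients without any post-operative PCS.
5. Keep the comparison of completers and drop-outs, by arm, as description only.

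The cost is a change of wording and modest programming. No new data are needed.

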##### Self-care Program Cost Analysis

An estimate of the annual cost of developing and refining the self-care program will be calculated from the perspective of the surgeon's office at one point in time. Intervention program logs will be used to estimate the recurring labor and operational costs of delivering the program. Because the research team will have delivered the program to 90 patients, we will calculate the telephone counselor time, phone costs, and print material costs per patient required to prepare and deliver telephone and in-hospital sessions. In addition, we will estimate the cost of behavioral expert supervision. Sensitivity analyses will test the range of assumptions for telephone counselor time and salary, print material costs, and clerical scheduling time. This secondary analysis will serve future dissemination discussions.

## Conclusion

This paper presented the theoretical rationale and design of an ongoing randomized controlled trial that will test the efficacy of a Patient Self-Management Support intervention on TKR functional outcomes. TKR is a common and well accepted intervention for advanced knee arthritis and, thus, maximizing functional outcomes is of utmost priority. If efficacious, this intervention has considerable potential for dissemination. In addition to the potential for patient support programs to enhance self-management, lessons learned in this trial may inform tailored post-TKR rehabilitation strategies, including home activity and exercise regimens.
